#### 3.4.2 Treatment Assignment

Patients will be assigned to treatment groups in a randomized fashion. Drugs will be numbered in such a way that patients at each investigational site will receive the treatment sequentially as they qualified to be randomized at Visit 3. The patient randomization number will be the lowest available treatment number.

#### 3.4.3 Blinding

There will be three sets of sealed envelopes containing the randomization codes that will be generated by an external consultant. One set will be provided to the packaging supplier, another will be provided to the investigator, and another will be kept at PharmaResearch Corporation.

The randomized code will be broken ONLY in case of an emergency. If possible, the investigator must contact the Sponsor or designee before unblinding the code to discuss the event leading to potential unblinding such as a possibly drug-related serious adverse event.

Randomization data are kept strictly confidential, accessible only to authorized persons, until the time of unblinding. At the conclusion of the trial, the occurrence of any emergency code breaks will be verified after return of all code break reports and unused drug supplies to Theratechnologies. Only when the study has been completed, the data file verified, and the protocol violations determined, will the drug codes be broken and made available for data analysis.

[For details of the emergency procedure for unblinding of individual patients in cases of emergency see section 6.2.]

#### 3.4.4 Concomitant Therapy

Oral or parenteral glucocorticoids will not be permitted during the study. Hormone replacement therapy for female subjects will be allowed. All other concomitant drugs should be maintained at constant dose during the study, if possible. Concomitant drugs will be recorded in the Case Report Forms.

Dose adjustments for insulin and/or oral hypoglycemics during the conduct of the trial will be at the discretion of the investigators.

#### 3.4.5 Treatment Compliance

Compliance will be checked by counting the number of empty vials returned at each visit.

### 3.5 Visit Schedule and Assessments

The schedule of assessments is presented in Appendix 1.

#### 3.5.1 Visit Schedule

Visits 1 and 2 are conducted prior to the baseline/randomization Visit 3, which is designated as Week 0.

##### VISIT 1: (Week -3, Screening)

- Obtain signed informed consent.
- Review inclusion and exclusion criteria.
- Obtain medical history.
- Review concomitant medications.
- Perform physical/neurological examinations (including screening for diabetic sensory neuropathy).
- Obtain 12-lead electrocardiogram.
- Obtain Vital signs (blood pressure, respiratory rate, pulse rate).
- Obtain body weight.
- Calculate body mass index.

- Perform funduscopy with dilation by optometrist or ophthalmologist (may be performed during the lead-in period) and examine for evidence of diabetic retinopathy (microaneurysms will not exclude the patient from participating in the study).
- Obtain blood for clinical laboratory screening tests (hematology, blood chemistry, lipid profile, and urinalysis-subjects with minimal proteinuria [ $<2+$ ] may continue with screening).
- Obtain blood for glycosylated hemoglobin (HbA1c) and insulin antibodies.
- Schedule mammography (for females) and prostate examination/PSA (for males) if not done within six months of screening.
- Collect 24-hour urine for albumin (may be performed during the lead-in period).
- Schedule Visit 2 to occur 6-8 days following Visit 1.

VISIT 2: (Week  $-2 \pm 1$  day, Start of lead-in period)

- Review inclusion and exclusion criteria.
- Assess adverse events.
- Review concomitant medications.
- Obtain body weight.
- Obtain vital signs (BP, RR, PR).
- Dispense diary (to monitor home blood glucose measurement, hypoglycemic episodes, study drug administration, **adjustments in oral hypoglycemic agents and/or insulin dosage**, diet, and exercise) and provide instructions regarding completion of the diary.
- Dispense home glucose meter with instructions.
- Dispense boxes of strips and lancets.
- Instruct the subject to withhold oral sulfonylurea, insulin, and other insulin secretagogues but he/she may take oral non-sulfonylurea hypoglycemic medication (if oral insulin sensitizer) in the morning of Visit 3.
- Instruct the subject to collect urine the day before the scheduled visit (starting at 6AM) until the morning (6AM) of the clinic visit.
- Dietician interview and assessment – caloric intake assessment, skin thickness (Harpenden), waist/hip measurements, and body fat mass (Lange).
- Schedule Visit 3 to occur 12-16 days after Visit 2.

VISIT 3: (Week  $0 \pm 2$  days, Baseline and Randomization)

- Review inclusion/exclusion criteria.
- Assess adverse events.
- Review concomitant medications.
- Obtain body weight.

- Obtain vital signs (BP, RR, PR).
- Perform physical/neurological examinations.
- Review/dispense diary. Subjects should be at least 90% compliant with the diary and diet in order to continue participation in the study.
- Replenish boxes of strips and lancets, if necessary
- Download home glucose readings from 14-day lead-in period.
- Instruct the subjects to call the clinic for any home blood glucose value that is >250 mg/dL.
- Dietician interview and assessment – caloric intake assessment, skin thickness (Harpenden), waist/hip measurements, and body fat mass (Lange).
- Collect 24-hour urine for creatinine and nitrogen.
- Obtain blood (fasting) for laboratory tests – IGF-1, IGFBP-1, IGFBP-3, sera for antibodies to insulin and TH9507, lipid profile, hematology, chemistry, HbA1c
- Perform oral 3-hr GTT with 75Gm Glucose (Glucola).
- Obtain blood for insulin and glucose levels every 30 minutes during OGTT.
- Assign randomized study treatment to subject.
- Administer first dose of blinded study drug in clinic at approximately noon.
- Dispense study drug supply for one week (8 doses).
- Instruct the subject to collect urine the day before the scheduled visit (starting at 6AM) until the morning (6AM) of the clinic visit.
- Schedule Visit 4 to occur 6-8 days following Visit 3.

#### VISIT 4: (Week 1 ± 1 day; Treatment Period)

- Assess adverse events.
- Review concomitant medications.
- Return all used and unused study drugs.
- Obtain body weight.
- Obtain vital signs (BP, RR, PR).
- Review/dispense diary.
- Download home glucose readings from previous 6-8 days.
- Replenish boxes of strips and lancets, if necessary.
- Collect 24-hour urine for creatinine and nitrogen.
- Obtain blood (fasting) for laboratory tests – IGF-1, IGFBP-1, IGFBP-3, lipid profile, hematology, chemistry.
- Perform oral 3-hr GTT with 75Gm Glucose (Glucola).
- Obtain blood for insulin and glucose levels every 30 minutes during OGTT.
- Administer blinded study drug while in clinic at approximately noon.
- Dispense study drug supply for three (3) weeks (24 doses).

- **Remind the subjects to call the clinic for any home blood glucose value that is >250 mg/dL.**
- Instruct the subject to withhold oral sulfonylurea, insulin, and other insulin secretagogues but he/she may take oral non-sulfonylurea hypoglycemic medication (if oral insulin sensitizer) in the morning of Visit 4.
- Instruct the subject to collect urine the day before the scheduled visit (starting at 6AM) until the morning (6AM) of the clinic visit.
- Schedule Visit 5 to occur 19-23 days after Visit 4.

VISIT 5 and VISIT 6: (Week 4  $\pm$  2 days and Week 8  $\pm$  3 days, Treatment period)

- Assess adverse events.
- Review concomitant medications.
- Return all used and unused study drugs.
- Obtain body weight.
- Obtain vital signs (BP, RR, PR).
- Dietician interview and assessment – caloric intake assessment, skin thickness (Harpenden) , body fat mass (Lange); and waist/hip measurements.
- Review/dispense diary.
- Download home glucose readings for the period since the previous visit.
- Collect 24-hour urine for creatinine and nitrogen.
- Obtain blood for laboratory tests – IGF-1, IGFBP-1, IGFBP-3, lipid profile, hematology, chemistry, HbA1C.
- Perform oral 3-hr GTT with 75Gm Glucose (Glucola).
- Obtain blood for insulin and glucose levels every 30 minutes during OGTT.
- Administer daily dose of blinded study drug in clinic at approximately noon.
- Dispense study drug supply sufficient for four weeks (32 doses).
- Replenish boxes of strips and lancets, if necessary
- **Remind the subjects to call the clinic for any home blood glucose value that is >250 mg/dL.**
- Instruct the subject to withhold oral sulfonylurea, insulin, and other insulin secretagogues but he/she may take oral non-sulfonylurea hypoglycemic medication (if oral insulin sensitizer) in the morning of Visit 6 and Visit 7.
- Instruct the subject to collect urine the day before the scheduled visit (starting at 6AM) until the morning (6AM) of the clinic visit.
- Schedule Visit 6 to occur 25-31 days following Visit 5, OR
- Schedule Visit 7 to occur 25-31 days following Visit 6.

VISIT 7: (Week 12  $\pm$  3 days)

- Assess adverse events.
- Review concomitant medications.

- Return all used and unused study drugs.
- Obtain body weight.
- Obtain vital signs (BP, RR, PR).
- Determine body mass index.
- Perform funduscopy with dilation by optometrist or ophthalmologist (may be performed within 5 days of date of Visit 7).
- Perform physical/neurological examinations (including examination for diabetic sensory neuropathy).
- Review/dispense diary.
- Download home glucose readings from previous 4 weeks.
- Dietician interview and assessment – caloric intake assessment, skin thickness (Harpender), waist/hip measurements, and body fat mass (Lange).
- Collect 24-hour urine for creatinine and nitrogen.
- Obtain blood (fasting) for laboratory tests – IGF-1, IGFBP-1, IGFBP-3, serum for TH9507 antibody, lipid profile, hematology, chemistry, HbA1C.
- Perform oral 3-hr GTT with 75Gm Glucose (Glucola).
- Obtain blood for insulin and glucose levels every 30 minutes during OGTT
- **Remind the subjects to call the clinic for any home blood glucose value that is >250 mg/dL.**
- **Investigator completes global assessment of diabetes control**
- Replenish boxes of strips and lancets, if necessary
- Subject receives NO STUDY DRUG AT THIS VISIT.
- Schedule Visit 8 (Post-treatment Visit) to occur 25-31 days following Visit 7.

VISIT 8: (Week 16 ± 3 days; Follow-up Visit; 16 weeks after randomization; 4 weeks post-treatment)

- Assess adverse events.
- Review concomitant medications
- Obtain body weight.
- Obtain vital signs (BP, RR, PR).
- Obtain blood for laboratory tests (hematology; blood chemistry; lipid profile)
- Collect urine for urinalysis.
- Schedule mammography (for females) and prostate examination/PSA (for males).
- Dietician interview and assessment – caloric intake assessment, skin thickness (Harpender) , body fat mass (Lange), and waist/hip measurements.
- Review diary.
- Download home glucose readings for the period since Visit 7.

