#### 3.5.2.3.6 Oral Glucose Tolerance Test (OGTT) with paired glucose and insulin levels

Blood glucose and insulin will be measured at 0 minutes (prior to ingestion of glucose), 30 minutes, 1, 1.5, 2, 2.5, and 3 hours. For these determinations, oral sulfonylureas, insulin, and other insulin secretagogues must be withheld on the morning of the OGTT. Insulin sensitizers need not be withheld at such times.

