## 4. Statistical Methods

### 4.1 Statistical Methods to be Employed

#### 4.1.1 Study Objectives

This is a Phase II, placebo-controlled, comparative study. The primary objective is to evaluate the safety of two doses (1 mg and 2 mg by daily subcutaneous injection) of TH9507 relative to placebo administration, over a 12-week period in patients with stable, type 2 diabetes.

The primary endpoint is the change in relative insulin response following the oral ingestion of glucose over the 12-week treatment period. The relative insulin response is defined as the ratio of the incremental plasma insulin response above basal at 30 minutes to that of plasma glucose, divided by basal plasma insulin levels.

The secondary objectives are to evaluate the effects of 12 weeks of daily treatment with TH9507 on HbA1c, blood glucose measurements, **use of oral hypoglycemic agents and/or insulin and control of diabetes.**

The secondary endpoints include the change in HbA1c at Week 12 compared to baseline and changes in mean daily serum glucose concentrations compared to the 14 day lead-in period values, **changes in the number of dose adjustments per week for insulin and/or oral hypoglycemic agents compared to the 14 day lead-in period, and the number of subjects with a change in the control of diabetes.**

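### The visit list gives no timely drug-withholding instruction for the Week 1 glucose tolerance test, and the Visit 4 instruction names Visit 4 where Visit 5 is evidently meant

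*Protocol*

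**What the plan says.** Protocol Section 3.5.2.3.6 sets a general rule for the OGTT: oral sulfonylureas, "insulin, and other insulin secretagogues must be withheld on the morning of the OGTT". Insulin sensitizers may be continued. OGTTs are listed at Visits 3, 4, 5, 6 and 7 (Weeks 0, 1, 4, 8 and 12), the five time points at which Section 4.1.5 has the primary endpoint calculated.

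The visit lists in Section 3.5.1 turn the rule into instructions to the patient:

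- **Visit 2** tells the patient to withhold "in the morning of Visit 3".
- **Visit 3** has no withholding bullet. It does carry the urine-collection instruction for the next visit and "Schedule Visit 4 to occur 6-8 days following Visit 3".
- **Visit 4** has the withholding bullet, but says the patient "may take oral non-sulfonylurea hypoglycemic medication (if oral insulin sensitizer) in the morning of Visit 4". Two bullets later comes "Schedule Visit 5 to occur 19-23 days after Visit 4".
- **Visits 5 and 6** (a joint list) tell the patient to withhold "in the morning of Visit 6 and Visit 7".

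Section 3.5 adds: "The schedule of assessments is presented in Appendix 1". That appendix is not in the text available for this review.

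**The concern.** These drugs are taken at home before the patient comes to clinic, so the instruction is useful only if it is given at the preceding visit or earlier. The protocol follows that pattern for three of the five tests and breaks it for the other two.

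The condition of measurement matters because Section 4.1.1 defines the primary endpoint as "the ratio of the incremental plasma insulin response above basal at 30 minutes to that of plasma glucose, divided by basal plasma insulin levels". Insulin or a secretagogue taken that morning can alter the basal insulin in the denominator as well as the 30-minute insulin and glucose increments. Weeks 1 and 4 are two of the four post-baseline points in the repeated-measures analysis. Tests done partly under withheld and partly under unwithheld medication would add avoidable noise, in all arms alike.

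**Working it through.** **Matching each OGTT to an instruction given at the preceding visit (Section 3.5.1)**

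| OGTT | Week | List that should instruct | Visit named there | Timely? |
|---|---|---|---|---|
| Visit 3 | 0 | Visit 2 | Visit 3 | Yes |
| Visit 4 | 1 | Visit 3 | no bullet | No |
| Visit 5 | 4 | Visit 4 | Visit 4 | Not as written |
| Visit 6 | 8 | Visit 5 | Visit 6 | Yes |
| Visit 7 | 12 | Visit 6 | Visit 7 | Yes |

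Three of five tests have a correct advance instruction. No bullet anywhere names Visit 5.

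**What the Visit 4 bullet means.** Every other withholding bullet names a coming visit. This one stands among next-visit instructions, after the OGTT of the same visit and just before the scheduling of Visit 5. A wrong visit number is the natural explanation. The alternative is that the number is right and the bullet belongs in the Visit 3 list. In that case Visit 4 lacks the instruction for Visit 5. Either way the two lists need the same corrected text.

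**Ceilings on exposure.** The plan states no figure to reproduce. The inputs are 45 randomized patients and 39 expected completers (Section 4.1.5), four post-baseline OGTTs, and the enrollment cap in Section 4.1.6 (33 in the larger insulin-use group, about 12 in the smaller).

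- Planned post-baseline tests: 4 × 45 = 180.
- Bullet read as Visit 5, so that only Week 1 lacks a reminder: 45/180 = 25%.
- Bullet read literally, so that Weeks 1 and 4 both lack one: (45 + 45)/180 = 90/180 = 50%.

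Insulin users all take a drug on the withholding list. If the cap is applied they number about 12 to 33. Sulfonylurea and other secretagogue users would add to this, but the protocol gives no count of them. For insulin users alone:

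- Week 1 only: 12/180 = 7% to 33/180 = 18%.
- Weeks 1 and 4: 24/180 = 13% to 66/180 = 37%.

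**Reach to Week 12.** Observed Week 0 and Week 12 tests both have correct advance instructions, so neither is exposed. The only route to Week 12 is the secondary last-observation-carried-forward analysis (Section 4.1.12). Expected non-completers are 45 − 39 = 6. If all six had Week 1 or Week 4 as their last OGTT, 6/45 = 13% of Week 12 values would be carried from an exposed visit. If the bullet is read as Visit 5, only those whose last test was Week 1 count.

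These are upper limits. They would be reached only if every site omitted the instruction and every patient counted took a drug that should have been withheld. No rate of unwithheld doses is assumed.

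**The case against.** The strongest reply is that the operative rule is intact. Section 3.5.2.3.6 is mandatory, has no exceptions by visit, and covers Weeks 1 and 4. Nothing in the visit list permits what it forbids. That stands, and it is why the point is minor. But the rule does not say when the patient is to be told. The visit list does, and it repeats the instruction visit by visit.

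A second reply is that both reminders fail only on an implausible reading. A sensible site takes the Visit 4 bullet either as Visit 5, leaving Week 1 uncovered, or as a misplaced Visit 3 bullet, leaving Week 4 uncovered. This also largely stands: one visit (25%) is the realistic ceiling, and 50% needs the literal reading by a site working strictly from each visit's list.

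Third, there are safeguards. Patients were told at Visit 2 to withhold before the Week 0 test, about a week before Visit 4. Concomitant medications and the diary are reviewed at Visits 4 and 5, and Section 4.1.11 provides a deviation category for concomitant medication. These make an unwithheld dose less likely or more likely to be noticed, but a review at the visit comes after the dose has been taken.

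Finally, Appendix 1 may repeat the instruction. That cannot be excluded, so the point is confined to the visit list. No appendix would make the visit number in the Visit 4 bullet right.

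**Conclusion.** The point holds and is minor. As written, the visit list carries out the withholding rule for three of the five OGTTs. The Week 1 instruction is missing from the Visit 3 list, and the Visit 4 instruction names the wrong visit.

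The realistic exposure is one intermediate visit, at most a quarter of planned post-baseline tests; the literal reading doubles that. The likely effect is added noise of unknown size in all arms. No bias between arms is claimed, and the observed Week 0 to Week 12 change is unaffected. The insulin-user ranges assume that the optional enrollment cap is applied. Confidence is high for the wording of the lists; how many tests would be affected in practice cannot be derived from the protocol.

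**What to change.** In Section 3.5.1:

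1. Add the withholding bullet to the Visit 3 list, directed at the morning of Visit 4.
2. In the Visit 4 withholding bullet, change the visit number from 4 to 5.

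All five OGTTs then have an instruction at the preceding visit. The cost is one added bullet and one changed number, with no change to design, sample size or analysis.

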### 3.5.2 Safety Assessments

This is a study to assess the safety of 12 weeks of daily administration of TH9507. Safety assessments will include the monitoring and recording of all adverse events and any serious adverse events; the sequential assessment of hematology, blood chemistry, and urinalysis parameters; the monthly monitoring of HbA1c, periodic assessments of lipid profiles, including HDL, LDL, total cholesterol, and triglycerides; monitoring for antibodies to TH9507 before and after 12 weeks of treatment; and periodic measurements of blood pressure, as well as performance of physical examinations including screening testing for diabetic sensory neuropathy. This study will seek to assess any clinically meaningful changes in insulin sensitivity through use of sequential periodic oral glucose tolerance tests with paired insulin and glucose levels to determine insulin:glucose ratios.

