#### 4.1.9 Strategy for Statistical Analysis

The safety population is defined as all subjects who were randomized and received at least one dose of study medication (1 mg TH9507, 2 mg TH9507, or placebo) during the course of the trial. This is the primary population for analysis.

The change from baseline values for biochemical laboratory parameters (secondary endpoints) will be analyzed using analysis of variance techniques (ANOVA) which focus on the between (different regimens) and within (same regimen) comparisons of these measurements over time, with center and insulin use group included as fixed effects. Analyses may be conducted as repeated measures analyses or individual analyses of specific study visits.

Glucose values will be obtained at home four times per day using a standardized glucose meter. Subjects will record glucose values in their diary. Glucose values, downloaded electronically from the glucose meters, will be used for statistical analysis.

The assessment of safety will be based mainly on the frequency of adverse events and on the number of laboratory values that fall outside of predetermined ranges. Other safety data (e.g. vital signs, special tests) will be considered as appropriate.

Adverse events will be summarized by presenting, for each treatment group, the number and percentage of subjects having any adverse event, having an adverse event in each body system and having each individual adverse event. Any other information collected (e.g. severity or relatedness to study medication) will be used to categorize the adverse event data as appropriate.

Laboratory data will be summarized by presenting shift tables using extended normal ranges (baseline to most extreme post-baseline value) by presenting summary statistics of raw data and change from baseline values (means, medians, standard deviations, ranges) and by flagging of notable values in data listings.

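### The visit lists schedule no urinalysis and no urine albumin on treatment, which does not fit the sequential urinalysis of section 3.5.2 and leaves the urinalysis shift table with one off-drug value

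*Protocol*

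**What the plan says.** Protocol section 3.5.2 opens with the purpose of the study: "This is a study to assess the safety of 12 weeks of daily administration of TH9507". It then lists the safety assessments, including "the sequential assessment of hematology, blood chemistry, and urinalysis parameters". Section 3.5.2.3.3 defines the urinalysis panel, which includes protein, glucose, ketones and red cells. Section 3.5.2.3.4 names the 24-hour urine tests: albumin, creatinine, nitrogen and total volume.

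The visit lists in section 3.5.1 give the timing:

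- **Visit 1 (Week -3):** urinalysis is part of the screening laboratory item, "Obtain blood for clinical laboratory screening tests (hematology, blood chemistry, lipid profile, and urinalysis-subjects with minimal proteinuria". Albumin is a separate item: "Collect 24-hour urine for albumin (may be performed during the lead-in period".
- **Visit 3 (Week 0, baseline):** the blood tests include "sera for antibodies to insulin and TH9507, lipid profile, hematology, chemistry". The urine item is the 24-hour collection for creatinine and nitrogen.
- **Visits 4 to 7 (Weeks 1, 4, 8 and 12):** blood tests again include hematology and chemistry, and the urine item is "Collect 24-hour urine for creatinine and nitrogen".
- **Visit 8 (Week 16, headed as four weeks post-treatment):** "Collect urine for urinalysis".

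Section 4.1.9 bases the safety assessment mainly on adverse events and on laboratory values outside preset ranges. It plans laboratory shift tables running from "baseline to most extreme post-baseline value".

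**The concern.** Section 3.5.2 puts hematology, chemistry and urinalysis in one phrase and calls all three sequential. The visit lists follow the first two through treatment and do not follow the third.

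At stake is what the urinalysis shift table can show. With the only scheduled post-baseline value taken four weeks after treatment, the table would look like a summary of treatment while describing the state after withdrawal. An asymptomatic change in urine protein, ketones or red cells during dosing could leave no trace. Adverse-event reporting is not a reliable backstop, because section 3.5.2.1 says that abnormal laboratory values are generally not recorded as adverse events unless they cause signs or symptoms or need treatment.

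The protocol itself treats urine protein as relevant: it excludes subjects on albuminuria (section 3.3.2) and sets a proteinuria limit at screening (Visit 1).

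**Working it through.** There is no sample size, power or error-rate figure to reproduce. The check is a count of each laboratory item in the visit lists of section 3.5.1.

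| Visit | Week | Hematology and chemistry | Urinalysis | 24-h creatinine and nitrogen | 24-h albumin |
|---|---|---|---|---|---|
| 1 | -3 | yes | yes | no | yes (or during lead-in) |
| 2 | -2 | no | no | no | no separate item |
| 3 | 0, before first dose | yes | no | yes | no |
| 4 | 1 | yes | no | yes | no |
| 5 | 4 | yes | no | yes | no |
| 6 | 8 | yes | no | yes | no |
| 7 | 12 | yes | no | yes | no |
| 8 | 16, post-treatment | yes | yes | no | no |

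**Counts**

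- Hematology and chemistry: 7 of 8 visits, 4 of the 4 on-treatment visits.
- Urinalysis: 2 of 8 visits, 0 of the 4 on-treatment visits.
- 24-hour creatinine and nitrogen: 5 of 8 visits, 4 of the 4 on-treatment visits.
- 24-hour albumin: one collection, 0 of the 4 on-treatment visits and none after the first dose.

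Visit 3 is not counted as on treatment. Its samples are the baseline, and the first dose is given at about noon that day, after the glucose tolerance test.

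**Consequence for section 4.1.9**

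1. The shift table compares baseline with the most extreme later value.
2. For urinalysis, the last scheduled value before dosing is at Week -3, because Visit 3 lists none.
3. The scheduled later values number one, at Visit 8. Visit 8 falls 25 to 31 days after Visit 7, and no study drug is given at Visit 7.
4. The most extreme of one value is that value. A change that appears at Weeks 1 to 12 and has cleared by Week 16 therefore gives no shift.
5. For urine albumin there is no later value, so no change can be computed.

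**The case against.** The strongest objection is that the schedule of assessments is in Appendix 1 (section 3.5), which is not in the text reviewed. It may list further urinalyses. The visit lists are also loosely drafted: urinalysis at Visit 1 sits in an item about drawing blood, and total urine volume appears in no visit list. This stands as a limit on the finding. If Appendix 1 does list urinalysis on treatment, it disagrees with the detailed visit lists, and the two still have to be reconciled.

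A reader might infer more than the documents support:

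- **That there are no on-treatment urine safety data at all.** This is wrong. 24-hour creatinine and nitrogen are collected at Weeks 1, 4, 8 and 12, and section 3.5.2.3.4 lists them among the safety laboratory evaluations.
- **That the protocol promises urinalysis throughout the 12 weeks.** Section 3.5.2 gives no frequency for it. The 12 weeks there is the length of dosing. The same sentence does give a timing for HbA1c and for TH9507 antibodies. The mismatch is a poor fit with the word sequential, not a broken numerical commitment.
- **That albumin monitoring was promised.** It was not. Albumin serves an exclusion criterion, and a single pre-treatment test is consistent with that use. Adding it on treatment is a recommendation.
- **That harm to glucose control would be missed.** Home glucose four times daily, glucose tolerance tests at Weeks 1, 4, 8 and 12, HbA1c at Weeks 4, 8 and 12, and chemistry glucose cover it. Serum creatinine and urea are also in the chemistry panel. The gap is urine protein or albumin, ketones and red cells.
- **That the 8-hour half-life in section 1 proves Visit 8 shows only recovery.** That figure is from plasma in vitro. It does not bound how long IGF-1-mediated or renal effects last. The point needs only the protocol's own description of Visit 8 as post-treatment.

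It is also fair to say that the rules for choosing shift-table values may be left to a SAP. A SAP can define which values count, but it cannot supply values that were never scheduled.

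**Conclusion.** The narrower point holds. As the visit lists stand, 0 of 4 on-treatment visits carry urinalysis or urine albumin, and the urinalysis shift table has one scheduled post-baseline value, taken off drug. That fits poorly with sequential urinalysis in a trial whose primary objective is safety during dosing.

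The conclusion assumes that the visit lists govern what is collected and that Appendix 1 adds nothing. It concerns scheduled tests only, as a site may run others. The primary endpoint is not affected. This is a gap worth closing in the safety data, limited to urine protein or albumin, ketones and red cells. It is not a failure of safety monitoring as a whole.

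**What to change.** 1. Reconcile the visit lists in section 3.5.1 with section 3.5.2 and Appendix 1, so that all three give the same urinalysis visits.
2. If Appendix 1 does not already list them, add the section 3.5.2.3.3 panel at Visit 3 (baseline) and at least Visit 7 (Week 12), and assay albumin in the 24-hour urine already collected at those visits.
3. Build the urinalysis shift table on on-treatment values, and report Visit 8 separately as off-drug follow-up.

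Cost: 45 subjects x 2 visits = 90 urinalysis panels and 90 albumin assays, slightly fewer with dropouts. Subjects already attend and bring urine at both visits, so there is no new visit or invasive procedure. The protocol does not say whether pooled 24-hour urine suits the urinalysis panel. If it does not, a spot sample at the same visit is needed.
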